**Methods::**

The study is a single-blind, parallel-group, randomized controlled clinical trial consisting of a 4-to-6-week treatment period and a 6-month follow-up period. Included participants will be randomized into three groups and given a treatment regimen of acupuncture, qianliean suppository, respectively. Patients in each group will be treated for 1 month as a course of treatment. The clinical efficacy and changes in inflammatory factor levels in each group will be assessed at the end of treatment.

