## Introduction

1

Chronic prostatitis (CP) is the most common genitourinary disorder in adult men. Surveys have shown that 35% to 50% of men will be affected by prostatitis at some point in their lives.^[1]^ CP is a difficult class of disease to treat. The typical clinical presentation of the disease is prolonged and recurrent pain in the pelvic region. The duration of the painful discomfort is often greater than 3 months. Some patients also often have varying degrees of urinary symptoms and sexual dysfunction.^[2,3]^ CP is a complex and protracted disease, which is difficult to treat. It brings serious psychological and economic burdens to patients and seriously affects their quality of life. Some patients even develop severe anxiety and depression as a result, which in turn leads to many social problems. Currently, it has attracted the attention of clinicians in various countries. In recent years, Western medical treatment of CP has gradually changed from antibiotics to a combination of α-blockers, androgens, anti-anxiety and antidepressants, and the efficacy has improved, but patients are still not satisfied with the treatment effect.^[4]^ Therefore, it is often necessary to continuously increase the dose of medication in order to achieve a more satisfactory therapeutic effect. This may cause serious adverse effects and affect patient compliance with treatment. Based on the above status, more effective treatment modalities need to be further explored.^[5]^ As a traditional treatment modality inherited for thousands of years, acupuncture has been valued and widely used in the clinical treatment of CP in recent years.^[6]^ This treatment modality can improve the quality of life by promoting neuromuscular excitability and by enhancing the contractility of urethral muscles and perineal muscles. qianliean suppository is a topical preparation made from several Chinese herbs with the effects of clearing heat, relieving dampness, promoting laxity, resolving siltation, dispersing nodules, and relieving pain. This study will investigate the therapeutic effects of acupuncture combined with qianliean suppository on CP, aiming to provide valuable evidence-based medical evidence for clinicians.

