### Interventions

2.4

(1)Acupuncture group: selected acupoints: *Shensu, Zhongliao, Huiyang, and Sanyinjiao* (all taken bilaterally). The acupuncture points will be positioned with reference to the 2006 National Standard of the People's Republic of China (GB/T 12346–2006) “Name and Positioning of Acupuncture Points”. After local sterilization of the acupoints, Shensu and Sanyinjiao will be needled with 0.3 × 40 mm milli-needles at a depth of 20 to 30 mm; Zhongliao and Huiyang will be needled with 0.3 × 75 mm milli-needles at a depth of 50 to 70 mm; the needles will be retained for 30 minutes.(2)Qianliean suppository group: use prostate suppository (National Drug Administration Z10980066, specification 2g × 5 s) for treatment. This product is brown or black-brown torpedo type suppository. Usage: The drug is inserted into the anus at night before bedtime, placed at a depth of 2 cm, 1 capsule each time, once a day. The ingredients of this drug are: extracts of Chinese herbs such as *Huangbai, Huzhang, Zhizi, Dahuang, Zelan, Maodongqing, Wuzhuyu, Weilingxian, Shichangpu and Lizihe*. Precautions for use: After the suppository is inserted into the anus, if there are uncomfortable symptoms such as bowel movement, abdominal pain and diarrhea, the method of use can be improved, such as applying vegetable oil outside the suppository or placing the suppository deeper, after the rectum adapts, the above symptoms can be reduced or disappear.(3)Combination therapy group: The treatment methods of (1) and (2) are combined.

Patients in each of the above groups will be treated for 1 month as a course of treatment. Patients in each group will be asked to abstain from sexual intercourse during the treatment period, to ensure the cleanliness of the perineal area, to observe the adverse reactions and to provide timely and effective treatment to ensure the treatment effect.

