### Statistical analyses

2.7

The case information collected by Excel will be imported into SPSS 25.0 statistical software to establish the analysis database and complete the statistical analysis of the data. Normality test will be performed by Kolmogorov-Smirnov method; chi-square test will be performed by Levene method. The measurement data conform to normal distribution and will be described by means and standard deviations, and comparisons between groups will be made by one-way ANOVA ANOVA or independent samples *t*-test; two-way comparisons will be made by Bonferroni method corrected *P*-value; not conforming to normal distribution, the measurement data will be described by medians and quartiles, and comparisons between groups will be made by Kruskal-Wallis method test or The Mann-Whitney *U* test will be used for comparison between groups, and the Dunnett's method will be used for comparison between two groups. The dichotomous data will be expressed as composition ratio and frequency in describing the distribution pattern, and the chi-square test and exact Fisher test will be used for comparison between groups. NIH-CPSI scores, mean urine flow rate and maximum urine flow rate will be compared between the two groups of patients at different time points using repeated measures ANOVA-generalized linear model equations.

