For the treatment of this disease, the common treatment options can be divided into pharmacotherapy (α-blockers, antibiotics, analgesics and botanicals), physiotherapy (biofeedback, microwave therapy, acupuncture) and surgery. Several randomized controlled trials and Meta-analyses have shown acupuncture to be effective in CP^[11–13]^ and a relatively safe treatment. Studies have shown that acupuncture can improve patients’ symptoms, reduce patients’ NIH-CPSI scores and decrease the number of white blood cells.^[14]^ However, there is still a lack of systematic and comprehensive clinical studies on acupuncture for the treatment of this disease, and most trials lack follow-up to understand the long-term efficacy. Therefore, this study will objectively evaluate the short-term and long-term clinical efficacy of different treatment regimens and the effect on the level of inflammatory factors in the organism by designing a standardized clinical trial with an acupuncture group and a Qianliean suppository group with NIH-CPSI scale score as the main outcome index, combined with a long follow-up. This study hopes to provide more ideas for the clinical treatment of CP.

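### For the effective rate, section 2.7 names only a between-groups chi-square/Fisher test, and for no outcome does it name the two contrasts on which a combination claim would rest

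*Protocol article*

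**What the plan says.** All references are to the protocol article.

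- **Aim.** The Introduction states: "This study will investigate the therapeutic effects of acupuncture combined with qianliean suppository on CP". The Discussion is broader: the study is to "objectively evaluate the short-term and long-term clinical efficacy of different treatment regimens". That sentence goes on to name only the acupuncture and suppository groups, with the NIH-CPSI score as the main outcome index.
- **Arms.** The abstract says "Included participants will be randomized into three groups". Section 2.4 lists acupuncture, the suppository and a third arm: "Combination therapy group: The treatment methods of (1) and (2) are combined". It lists no untreated or sham arm.
- **Dichotomous data.** Section 2.7 says "the chi-square test and exact Fisher test will be used for comparison between groups". It adds no pairwise step, contrast or correction. The total effective rate, defined under the primary outcome heading (2.5.1), is of this type.
- **Continuous data.** Section 2.7 says "comparisons between groups will be made by one-way ANOVA ANOVA or independent samples" t-tests, and then "two-way comparisons will be made by Bonferroni method corrected" P-values. For non-normal data it names Kruskal-Wallis or Mann-Whitney tests, and "the Dunnett's method will be used for comparison between two groups".
- **Repeated measures.** The last sentence of 2.7 compares NIH-CPSI and urine flow rates over time, but is written for two groups of patients.

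**The concern.** With these three arms, the only way to learn what the combination contributes is to compare it with acupuncture alone and with the suppository alone. Section 2.7 does not say that these two comparisons carry the combination claim. For the effective rate it names no two-group comparison at all.

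A chi-square test on the 3x2 table has the null that all three rates are equal. If one single treatment is weaker than the other, and the combination merely matches the better one, that null is false and the test tends to reject. A reader of the results could then take a significant between-groups P-value as support for the combination, when one component does all the work.

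For continuous outcomes the risk is smaller, because corrected pairs are planned. But the three pairs have equal standing, so a significant result for combination versus the weaker component alone could be presented as a combination effect. For NIH-CPSI, the repeated-measures sentence does not say which two of the three arms it compares.

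**Working it through.** The article gives no sample size, significance level, power or expected rates, so it has no figure to reproduce. Assumptions throughout: two-sided 0.05, equal arms of 30, 40, 60 or 100, and illustrative effects.

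**1. Three-arm chi-square when the combination adds nothing.** Rates: one single treatment 60%, the other 80%, combination 80%.

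Noncentrality = n × Σ(pᵢ − p̄)² / [p̄(1 − p̄)], on 2 degrees of freedom.

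- p̄ = (0.60 + 0.80 + 0.80)/3 = 0.7333
- Σ(pᵢ − p̄)² = 0.01778 + 0.00444 + 0.00444 = 0.02667
- p̄(1 − p̄) = 0.19556, so noncentrality = 0.1364 × n

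| n per arm | noncentrality | rejects, formula | rejects, simulation (40,000 runs) |
|---|---|---|---|
| 30 | 4.09 | 42.4% | 41.6% |
| 40 | 5.45 | 54.1% | 53.5% |
| 60 | 8.18 | 72.8% | 72.1% |
| 100 | 13.64 | 92.1% | 91.1% |

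Range over other assumed rates, 30 to 100 per arm: 60/70/70 gives 13% to 32%; 50/80/80 gives 75% to almost 100%.

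**2. Requiring the combination to beat both single treatments, same 60/80/80 setting.** With pooled two-proportion z tests, a false claim occurs in 2.2% to 2.5% of trials with each test at two-sided 0.05, and in 0.6% to 0.8% with each at 0.05/3. Over all the no-added-benefit settings run, the rule at 0.05 stayed at or below about 2.6%. This is expected: a false claim requires the test against the better component to err in the combination's favour, which has probability about 0.05/2 = 2.5%. Asking for the second success as well can only lower it. Hence no correction between these two tests is needed for a both-must-succeed claim.

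**3. Continuous analogue.** Means 0, 0.5 and 0.5 SD, combination equal to the better component, 20,000 runs.

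- One-way ANOVA rejects in 49%, 81% and 96% of trials at 30, 60 and 100 per arm.
- The planned Bonferroni pair, combination versus the better component, is falsely significant in the combination's favour in about 0.8%. This agrees with (0.05/3)/2 = 0.83%.

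**4. Power if the combination truly beats both.** Rates 65/65/85. Showing both at 0.05 each succeeds in 27%, 39%, 60% and 85% of trials at 30, 40, 60 and 100 per arm. With 0.05/3 each, it succeeds in 14%, 21%, 40% and 71%.

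**The case against.** **The plan is not only omnibus.** A reader might infer that the planned group tests are all three-arm omnibus tests. The article does not support that. Section 2.7 plans Bonferroni-corrected pairs and other two-group methods for continuous data. NIH-CPSI, the main outcome index, is of that type. This stands, and it confines the missing two-group step to dichotomous data.

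**Three-arm is a reading.** The chi-square sentence does not say 3x2 and could mean pairwise 2x2 tables. That also stands. On that reading, however, no correction is named and the decisive pairs remain unnamed, so the remedy is the same.

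**The percentages are not error rates.** In every scenario of steps 1 and 3 one single treatment really is worse, so rejecting equality of all three arms is right. A reader might take 42% to 91% as a false-positive rate; it is power against a false omnibus null. Harm arises only if that result is reported as evidence for the combination, and nothing in the article says it will be.

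**The aim is broader in the Discussion.** An omnibus test followed by corrected pairs is a standard approach to comparing several regimens, and the Discussion names the two single-treatment groups. So the documents do not support discarding the Bonferroni scheme or reducing acupuncture versus suppository to a descriptive result. But the Introduction states the combination as the subject, and a claim about it needs its own contrasts.

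**A fuller document may settle this.** The decisive contrast is often fixed in the full protocol or analysis plan, so silence alone would not be a finding. What remains is in the text itself: section 2.7 selects tests, gives a two-group step for one data type and not the other, and words a three-arm comparison for two groups.

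**Conclusion.** The point holds in a limited form. For the effective rate, the one named analysis, read across three arms, does not answer the question in the Introduction. It would reject in 42% (30 per arm) to 91% (100 per arm) of trials in which the combination adds nothing to the better single treatment, at assumed rates of 60/80/80. Over the wider range of assumed rates in step 1 the figures run from 13% to almost 100%. The rates and arm sizes are assumptions, since the article gives none.

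For continuous outcomes the planned Bonferroni pairs already limit a false claim over the better component to about 0.8%. What is lacking there is a statement of which pairs support a combination claim, and a repeated-measures sentence that fits three arms. The article does not show that the main outcome is unprotected or that the Bonferroni scheme is wrong.

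**What to change.** In section 2.7:

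1. Name combination versus acupuncture and combination versus suppository as the contrasts on which any combination claim rests, for every outcome used for that claim.
2. For the total effective rate, add these two comparisons as risk differences with 95% confidence intervals.
3. State that the combination is said to add benefit on an outcome only if it is better than both single treatments. If this both-must-succeed rule is adopted, each of the two tests can be done at two-sided 0.05 without correction between them.
4. Keep acupuncture versus suppository as a reported comparison, and keep the omnibus tests as supportive.
5. Reword the repeated-measures sentence for the three arms.

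The cost is wording, with no new data. The downside is that beating only one component no longer supports a claim of added benefit. The rule works outcome by outcome; it does not settle which outcome or time point carries the trial's main claim.

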### Study design and setting

2.1

The study is a single-blind, parallel-group, randomized controlled clinical trial consisting of a 4- to 6-week intervention and a 6-month follow-up period. The study will be conducted at one site, the Affiliated Hospital of Shaanxi University of Chinese Medicine. A brief flow chart of the entire study is shown in Figure 1. This study will adopt a parallel controlled design approach. We will ensure a balance of baseline data across groups by having an adequate sample size and a completely randomized grouping method. The study will be approved by the Ethics Committee of the Affiliated Hospital of Shaanxi University of Chinese Medicine. We will not begin recruiting participants until ethics committee approval has been obtained.

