#### Primary outcome measure

2.5.1

The CP symptom index (NIH-CPSI) with prostatitis-related sexual function index score will be performed before and after treatment. The changes of urodynamic indexes will be observed in each group before and after treatment, and the specific indexes included maximum urinary flow rate, maximum bladder capacity, maximum forced urinary muscle pressure and bladder stability. The observation times for the primary outcome indicators are shown in Table 1.

**Table 1 T1:** Treatment schedule and outcome measures.

Items	Before Treatment	Treatment period, twice a week, 8 times in total (treatment starts within 1 wk after registration)				Post observation Period
TIME POINT	Registration	wk 1	wk 2	wk 3	wk 4	1 wk later Treatment completion
Inclusion criteria	√					
Exclusion criteria	√					
Informed consent	√	√	√	√	√	√
Confirmation of subjective symptoms	√		√		√	√
Chronic prostatitis symptom index	√	√	√	√	√	√
prostatitis-related sexual function index Observation of adverse events	√		√		√	

Clinical efficacy evaluation criteria: significant effect: the symptoms of urinary disorder disappeared after treatment, no pain and discomfort, and normal sexual function will be restored at the same time; effective: the symptoms of urinary disorder basically disappeared, a little pain and discomfort existed, pain will be tolerated, and sexual function will be basically restored to normal; ineffective: the situation of urinary disorder did not improve, obvious pain and discomfort existed, and no significant change in sexual function will be seen. The total effective rate =  (the number of effective cases to the number of effective cases)/total cases × 100%.

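### The total effective rate is compared only by unadjusted chi-square or Fisher tests, although registration NIH-CPSI is planned for every man; these tests are valid but probably give up precision.

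*Protocol article*

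**What the plan says.** - **Test.** Protocol article, 2.7 Statistical analyses, on dichotomous data: "the chi-square test and exact Fisher test will be used for comparison between groups". No covariate or stratification factor is named. The only model in 2.7 is a repeated-measures one, for NIH-CPSI scores and urine flow rates. It does not mention the effective rate.
- **Outcome.** "The total effective rate" is defined in 2.5.1, the primary outcome section. The best category requires that "the symptoms of urinary disorder disappeared after treatment, no pain and discomfort, and normal sexual function will be restored at the same time". The middle category is a milder version of the same end state. The worst category reads "the situation of urinary disorder did not improve, obvious pain and discomfort existed, and no significant change in sexual function will be seen".
- **Baseline value.** Also in 2.5.1: "The CP symptom index (NIH-CPSI) with prostatitis-related sexual function index score will be performed before and after treatment". Table 1 ticks the symptom index at registration.
- **Allocation.** "Included participants will be randomized into three groups" (abstract, Methods). Section 2.1 relies for balance on an adequate but unquantified sample size and on "a completely randomized grouping method". Section 2.3 adds no stratification.
- **Main index.** The Discussion describes the trial as one "with NIH-CPSI scale score as the main outcome index".

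**The concern.** The two success categories mainly describe how a man is at the end of treatment, not how far he has moved. A man who enters with mild symptoms has less distance to cover. Section 2.2.2 sets no minimum NIH-CPSI, and the Introduction says that urinary and sexual symptoms affect only some patients and vary in degree, so severity at entry may differ widely. It is therefore plausible that baseline severity predicts response.

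If it does, two things follow. An analysis that ignores it has less power than the collected data allow. And in the one trial that is run, any chance difference in entry severity between arms stays in the estimated difference in response rates. Simple randomisation balances the arms only on average, and nothing else stated in the design or in 2.7 deals with imbalance for this outcome.

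**Working it through.** The article gives no sample size, alpha, power, expected rates or baseline-response correlation, so there is no stated figure to reproduce. Everything below rests on assumptions, shown over a range.

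**Assumptions.** Two-sided alpha 0.05; equal allocation; one pairwise comparison; no dropout; response means either of the two success categories; four pairs of response rates; latent correlation ρ between baseline severity and response from 0 to 0.7.

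**Step 1: sample size for about 80% unadjusted power.** With p̄ the mean of the two rates,

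n per arm = [1.96·√(2p̄(1−p̄)) + 0.8416·√(p1(1−p1) + p2(1−p2))]² / (p2−p1)²

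For 70% versus 90%: [1.96·√0.32 + 0.8416·√0.30]² / 0.04 = (1.109 + 0.461)² / 0.04 = 61.6, so 62. The other pairs give 93, 82 and 64.

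**Step 2: simulation, 6,000 trials per setting.** Baseline x and noise e are standard normal. The latent response is −ρx + √(1−ρ²)·e, and a man responds if this plus Φ⁻¹(p) exceeds 0, so the marginal response rate is p. The unadjusted analysis is the pooled chi-square test without continuity correction. The adjusted analysis is the likelihood-ratio test of arm in a logistic regression on arm and x. The Monte Carlo standard error of one power figure near 80% is √(0.8·0.2/6000), about 0.5 points.

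Power gained by adjustment, in percentage points:

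| Rates | n per arm | ρ=0 | 0.2 | 0.3 | 0.4 | 0.5 | 0.6 | 0.7 |
|---|---|---|---|---|---|---|---|---|
| 50 v 70% | 93 | 0.3 | 1.3 | 2.6 | 3.9 | 6.7 | 9.3 | 12.1 |
| 60 v 80% | 82 | 0.2 | 1.1 | 2.0 | 3.7 | 6.2 | 8.8 | 12.4 |
| 70 v 90% | 62 | 1.1 | 2.0 | 2.6 | 4.3 | 6.4 | 8.1 | 11.3 |
| 75 v 93% | 64 | 1.6 | 1.8 | 2.8 | 4.5 | 5.4 | 7.7 | 10.6 |

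From ρ = 0.3 to 0.6 the gain runs from 2.0 to 9.3 points. At ρ = 0 the covariate carries no information, so the 1.1 and 1.6 points in the last two rows reflect the switch of test (likelihood-ratio for Pearson) and not the adjustment. The low end of the range is therefore small.

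**Step 3: dependence on trial size (70% versus 90%).**

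| n per arm | Unadjusted power | Gain, ρ=0.3 | ρ=0.5 | ρ=0.6 |
|---|---|---|---|---|
| 30 | about 50% | 4.7 | 8.1 | 11.4 |
| 40 | about 63% | 2.4 | 5.9 | 9.7 |
| 60 | about 81% | 2.5 | 5.8 | 7.9 |
| 100 | about 95% | 0.7 | 1.7 | 2.9 |

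**Step 4: validity.** With 70% in both arms, 62 per arm and 8,000 trials, the unadjusted test rejects in 4.7% (ρ = 0.3) and 5.0% (ρ = 0.6) of trials; the adjusted test rejects in 5.1% and 5.0%.

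**Step 5: imbalance in one realised trial.** At an assumed 40 per arm, the 95% limit of the chance baseline difference is 1.96·√(2/40) = 0.44 SD. At a 70% rate the normal density at the threshold is 0.35, so with ρ = 0.5 that difference shifts the rate difference by about 0.35 × 0.5 × 0.44 = 0.077, or 8 points. This is the edge of the range, not a typical shift. For comparison, the standard error of the risk difference is √(2 × 0.21/40) = 0.10, so the ordinary 95% interval already spans about ±20 points, and that sampling error includes chance imbalance.

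**The case against.** Chi-square and Fisher tests are standard and valid, and covariates for a binary outcome are often left to a full protocol or analysis plan, neither of which is shown. The first half stands: this is a choice that can be improved, not an error or a contradiction. The second half carries less weight, because 2.7 does not leave the method open: it names the tests for this type of data.

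The more serious objection is that the article never says that response depends on NIH-CPSI. The efficacy categories use no score or cut-off, and the worst one is worded partly as change from the man's own starting point. The rate turns on the boundary with that category, so dependence on entry severity could be weaker than a pure end-state model implies, or could even differ in direction. The printed formula for the rate is also garbled in its numerator, so counting both success categories as response is a reading. This stands: prognostic strength is a plausible assumption, and the simulation is one model of it.

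Finally, the Discussion names the NIH-CPSI score as the main index, and that score has its own repeated-measures analysis. The effective rate is one of several measures under 2.5.1 and is not clearly the deciding one. This limits the consequences but does not change the recommendation.

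**Conclusion.** The point holds as one of efficiency and of precision in the realised trial. The effective rate has only an unadjusted comparison, a plausibly prognostic baseline value is already scheduled, and no stratification is stated. The likely gain from adjusting is about 2 to 9 points of power, given a correlation of 0.3 to 0.6 and about 80% unadjusted power. It is about 0 to 2 points at a correlation of 0 to 0.2. At a correlation of 0.6 (70% versus 90%) it ranges from 11.4 points at 30 per arm to 2.9 at 100.

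The documents do not support four stronger readings that a reader might infer:

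- **That the unadjusted test is invalid, or mistakes imbalance for effect too often.** Its simulated type I error is about 5%.
- **That a fixed 7 to 10 points of power are lost.** At about 80% unadjusted power that needs a correlation of roughly 0.55 to 0.65, and the article gives neither a correlation nor a sample size.
- **That the trial's conclusion rests on this rate.** The Discussion points to the NIH-CPSI score.
- **That bladder stability has the same problem.** The article does not say that it is dichotomous.

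**What to change.** In 2.7, prespecify logistic regression with arm and registration NIH-CPSI (as a continuous covariate) as the analysis of the total effective rate. Report the covariate-standardised risk difference with its 95% confidence interval for combination versus acupuncture alone and for combination versus suppository alone. Keep the chi-square or Fisher test as a supportive analysis.

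The change takes one or two sentences and slightly more analysis work. It needs no new data, because the covariate is already in Table 1. Fixing the covariate beforehand also rules out a choice to adjust made after any imbalance has been seen.

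### The only analysis naming NIH-CPSI compares two groups in a three-arm trial and leaves the tested term, the visit and the use of the registration score open

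*Protocol article*

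**What the plan says.** **Arms.** The Abstract (Methods) states: "Included participants will be randomized into three groups". Section 2.4 describes acupuncture, then the suppository, then the third arm: "Combination therapy group: The treatment methods of (1) and (2) are combined". The Introduction makes that third arm the subject of the trial: "This study will investigate the therapeutic effects of acupuncture combined with qianliean suppository on CP".

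**Main outcome.** The Discussion describes the trial as one "with NIH-CPSI scale score as the main outcome index, combined with a long follow-up", although there it mentions only an acupuncture group and a suppository group. Section 2.5.1 says: "The CP symptom index (NIH-CPSI) with prostatitis-related sexual function index score will be performed before and after treatment". In Table 1 the row "Chronic prostatitis symptom index" is ticked six times: registration, weeks 1 to 4, and one week after completion. The Abstract places the efficacy assessment at the end of treatment.

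**Analysis.** The last sentence of Section 2.7 takes NIH-CPSI together with two urine flow measures (mean and maximum) and says that these "will be compared between the two groups of patients at different time points using repeated measures ANOVA-generalized linear model equations". No other sentence ties NIH-CPSI to a method. Earlier, the same section gives a general rule for continuous data: one-way ANOVA or a t-test with Bonferroni-corrected pairwise comparisons, and rank tests where normality fails.

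**The concern.** The sentence does not fit the design. Two groups cannot describe a three-arm comparison, and nothing says which two are meant. If the pair is the one that the Discussion names, the arm left out is the combination.

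The sentence also leaves three choices open for the main outcome:

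- which term is the test (group, or group by time);
- which visit carries the conclusion;
- whether the registration score is a repeated level or a covariate.

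These choices lead to different estimates. The clinical question is whether the combination does better than each single treatment when treatment ends. A group effect averaged over visits that include registration answers a different question, and an omnibus interaction does not say which arm differs from which, or when. If nothing is fixed beforehand, the arms, the term and the visit can be chosen after the data are seen.

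**Working it through.** **1. Arms.** The Abstract and Section 2.4 give three; the NIH-CPSI sentence in Section 2.7 gives two. No reading of that sentence keeps all three arms separate.

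**2. Role of registration.** The text does not state it. One indication comes from urine flow. Section 2.5.1 observes the urodynamic indexes, including maximum flow, only before and after treatment. Flow can then be a repeated measure only if the pre-treatment value is one of its levels, and the same sentence governs NIH-CPSI. This makes registration as a repeated level the likely reading, but not a stated one.

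**3. Group main effect, if registration is a level.** Assume a linear onset, with shares 0, 0.25, 0.50, 0.75, 1 and 1 of the end-of-treatment difference at the six Table 1 visits.

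- Average effect: (0 + 0.25 + 0.50 + 0.75 + 1 + 1)/6 = 3.5/6 = 0.583, or 58%.
- Averaging also lowers the variance. With equal correlation 0.5 between visits (assumed), the variance factor is (1 + 5 × 0.5)/6 = 0.583.
- Standardised effect: 0.583/√0.583 = 0.76 of that at a single end-of-treatment visit.

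**4. Power by tested term.** The protocol states no power, sample size, SD or correlation, so there is no figure to reproduce. Assumptions: difference of 0.5 SD at end of treatment, two-sided 0.05, 63 per arm (80% power for an unadjusted end-of-treatment comparison), equal correlation 0.5. Onset patterns: immediate (full effect from week 1), gradual (as in step 3), late (0 to week 2, half at week 3, full from week 4).

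| Test | Immediate | Gradual | Late |
|---|---|---|---|
| Group main effect, registration as a level | 86% | 57% | 33% |
| Group by time, two groups | 81% | 81% | 94% |
| Group by time, three groups | 83% | 83% | 96% |
| Baseline-adjusted end-of-treatment contrast | 90% | 90% | 90% |

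At correlation 0.7 the group-by-time tests reach 97% or more, against 98% for the adjusted contrast. At correlation 0.3 with an immediate effect, the main-effect test beats the adjusted end-of-treatment contrast, 95% to 84%.

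**5. What the interaction tests.** With three arms and six visits it has (3 − 1) × (6 − 1) = 10 degrees of freedom; with two groups, 5. Either way it identifies no pair of arms and no visit.

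**6. Gain from using baseline.** Adjusting for a baseline with correlation r multiplies the variance of an unadjusted end-of-treatment comparison by 1 − r². If that comparison has 80% power at two-sided 0.05, adjusted power is Φ(2.80/√(1 − r²) − 1.96).

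| r (assumed) | 1 − r² | Power |
|---|---|---|
| 0.4 | 0.84 | 86% |
| 0.5 | 0.75 | 90% |
| 0.6 | 0.64 | 94% |
| 0.7 | 0.51 | 98% |

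The comparator here is an unadjusted post-treatment comparison, as the general ANOVA or t-test rule would give, not the repeated-measures ANOVA.

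**The case against.** The strongest reply is that the two-group wording is a slip. One-way ANOVA and Kruskal-Wallis in the same section suit three arms, and the general rule, applied to the end-of-treatment NIH-CPSI, would give Bonferroni-corrected pairwise tests. This is a condensed article, and details such as the covariance structure may properly sit in an analysis plan. Much of this stands: a reader might infer that the end-of-treatment contrasts are missed altogether, and the documents do not support that. But the general rule is not tied to NIH-CPSI, does not use baseline and designates no contrast as primary. A slip in the one sentence that governs the main outcome still has to be corrected.

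Other stronger readings also go too far:

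- *The plan counts baseline as an outcome.* Likely, but not stated.
- *The plan loses power.* Only under some combinations of tested term, onset and correlation. The group-by-time test loses little or nothing at moderate to high correlation.
- *Patients with a missing visit are deleted.* Section 2.6 carries the last observation forward for the main efficacy indicators in the full analysis set.
- *Flow has no repeated time points.* Before and after treatment are two.

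**Conclusion.** The sentence is wrong as written: it specifies a two-group analysis of the main outcome in a three-arm trial, and it fixes neither the tested term, nor the visit, nor the use of the registration score. That conclusion rests on the text alone.

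The numerical consequences are conditional. Dilution to 58% (76% on the standardised scale) requires registration as a repeated level, a group main-effect test and a linear onset; the 76% also requires correlation 0.5. The 86% to 98% shows what baseline adjustment could add over an unadjusted post-treatment comparison, per contrast and before any multiplicity correction. It is not a measured loss from the repeated-measures ANOVA. The documents give no input that would narrow these ranges.

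Nor do the documents show that the combination arm will in fact be left out. The sentence permits it, and that is enough reason to rewrite it.

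**What to change.** Replace the NIH-CPSI sentence in Section 2.7 with one model fixed in advance:

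- **Model.** Post-baseline NIH-CPSI on arm (three levels), visit, arm by visit and baseline NIH-CPSI, allowing for correlation between visits within a patient.
- **Primary contrasts.** Combination minus acupuncture and combination minus suppository, at one named visit. The Abstract points to the end of treatment; Table 1 offers week 4 and one week after completion, so state which.
- **Multiplicity.** Apply the plan's Bonferroni correction to these two contrasts (for an overall two-sided 0.05, assumed here, 0.05/2 = 0.025 each), with intervals at the matching level.
- **Missing scores.** State that the model uses observed scores, and keep the carried-forward rule of Section 2.6 as a sensitivity analysis.
- **Other outcomes.** For continuous outcomes measured only before and after treatment, such as urine flow, use ANCOVA on the pre-treatment value.

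The Discussion should also name all three arms. The cost is wording only: the registration and weekly scores are already scheduled in Table 1, and the planned software, SPSS 25.0, fits mixed models.
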